### Symptomatology

Data will be collected on patient pre-intervention disease-specific symptoms.. A dichotomic variable was created based in the presence or absence of any symptom.

### Complications

A checklist (yes/no) is used for complications throughout the course of the follow-up period (intra-surgical, during hospital admission, and up to 2 and 5 years after the intervention, including complications related to reconstructive surgery). When there is no information on complications in the medical record, it will be assumed that none occurred.

Surgical severity: We record the use of the following surgical techniques (ranked from least to most complex): conservative surgery (tumorectomy, quadrantectomy, and segmentectomy), simple mastectomy, radical mastectomy, modified radical mastectomy, skin-sparing mastectomy, nipple-sparing mastectomy, areola-sparing mastectomy, breast reconstruction and contralateral prophylactic mastectomy.

pTNM: Staging is performed following the American Joint Committee on Cancer [27, 28], being pTNM considered except for cases who received neoadyuvant therapy (cTNM).When there are no pTNM staging data, the analogous cTNM will be used, otherwise, missing value will be recorded. In cases of bilateral cancer, we will consider the final stage as a peak between right and left breast. In the cases of Tx, Nx or Mx, we will consider the disease to be T0, N0 or M0. If cM is missing, then cM will be considered to be 0.

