**Methods:**

Prospective cohort study involving 13 hospitals in Spain with a follow-up period of up to 5 years after diagnostic biopsy. Eligibility criteria: Patients diagnosed with breast cancer between April 2013 and May 2015 that have consented to participate in the study. Data collection: Data will be collected on the following: pre-intervention medical history, biological, clinical, and sociodemographic characteristics, mode of cancer detection, hospital admission, treatment, and outcomes up to 5 years after initial treatment. Questionnaires about quality of life (EuroQoL EQ-5D-5 L, the European Organization For Research And Treatment Of Cancer Core Quality Of Life Questionnaire EORTC QLQ-C30 join to the specific breast cancer module (QLQ-BR23), as well as Hospital Anxiety and Depression Scale were completed by the patients before the beginning of the initial treatment and at the end of follow-up period, 2 years later. The end-points of the study were changes in health-related quality of life, recurrence, complications and readmissions at 2 and 5 years after initial treatment. Statistical analysis: Descriptive statistics will be calculated and multivariate models will be used where appropriate to adjust for potential confounders. In order to create and validate a prediction model, split validation and bootstrapping will be performed. Cost analysis will be carried out from the perspective of a national health system.

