## Methods/Design

### Aim

The specific study objectives (which are set out in detail in Table 1) are, in brief: 1. to assess outcomes related to a) process of care (early diagnosis, access to health care and screening programs, delays in diagnosis, and variability in treatments), and b) patients (sociodemographic and clinical characteristics, including biomarkers, and patient-reported outcomes, such as quality of life and emotional state); 2. to create and validate prediction models (for changes in quality of life, relapse and death); and 3. to assess the costs associated with breast cancer care and its potential variations between Spanish regions.

**Table 1 Tab1:** Objectives

1. Outcomes assessment	2. Creation of predictive models	3. Health services evaluation in breast cancer patients in Spain
To describe and analyse variability in outcomes by mode of detection, hospital, region and surgeon	• To create and validate predictive rules for relapse, mortality and complications	• To estimate the average costs of breast cancer care in Spain
To describe and analyse variability in the diagnostic process and treatment	• To identify risk factors for poor health-related quality of life 2 years after treatment	• To investigate differences between Spanish regions
To explore potential inequalities by age, education and socioeconomic level	• To validate our predictive rules for relapse, mortality and complications in a retrospective sample of patients from early detection programs	• To identify the most efficient process and treatments in breast cancer
To evaluate the impact of first hospital care (urgent or scheduled) and of delays on relapse, metastasis and death		

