### Study population

Women older than 18 years with an incident breast tumor will be included. The breast cancer diagnosis considered will be that reached after a biopsy of the tumor, including cases of ductal carcinoma in situ, invasive ductal carcinoma, tubular carcinoma, mucinous carcinoma, papillary carcinoma, cribriform carcinoma, invasive lobular carcinoma and lobular carcinoma in situ.

Symptomatic breast cancer will be included, as well as screened and interval breast cancer. The breast cancer screening program is public and universal in Spain. Following the recommendations of the European Guidelines for Quality Assurance in breast cancer screening and diagnosis [14], the Spanish Breast Cancer Screening Program provides free biennial screening to women who are between 50 and 69 years old. Recently, women aged from 45 to 49 years and 65 to 69 years are being incorporated into screening programs. Interval breast cancer is defined as primary breast cancer diagnosed in a woman who had a screening test, with or without further assessment, with a negative result, and diagnosed well before the next invitation to the screening test or before a period of time equal to the screening interval in a woman who has reached the upper age limit for screening [15].

Exclusion criteria are: diagnosis of sarcoma, lymphoma or inflammatory carcinoma; breast cancer recurrence; terminal illness; and a severe mental or physical condition or any other factor which interferes with the woman’s ability to complete the questionnaires. In addition, in situ carcinomas will be excluded from the survival analysis.

Socio-demographic and clinical data will be collected on women lost to follow-up. Figure 1 represents flow-chart of the recruitment and Table 2 represents data collection in participant centers.

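### Unassessed T and N are recoded to T0 and N0, and undocumented complications to none; the complications rule is the more serious because it does not require the record to cover the follow-up window

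*Protocol article*

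**What the plan says.** The section headed Missing data assumptions and recoding of variables is followed by the Complications section, which contains both rules.

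- **Complications.** A yes/no checklist covers the operation, the admission, and follow-up to 2 and 5 years. Then: "When there is no information on complications in the medical record, it will be assumed that none occurred".
- **Stage, absent altogether.** "When there are no pTNM staging data, the analogous cTNM will be used, otherwise, missing value will be recorded".
- **Stage, component not assessable.** "In the cases of Tx, Nx or Mx, we will consider the disease to be T0, N0 or M0". A further sentence sets a missing clinical M to zero: "If cM is missing, then cM will be considered to be 0".

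Three other places show where these values are used.

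- The abstract lists as end-points "changes in health-related quality of life, recurrence, complications and readmissions at 2 and 5 years after initial treatment".
- Table 1 includes the aim "To create and validate predictive rules for relapse, mortality and complications". It also sets out to compare outcomes across hospitals, regions and surgeons.
- The Variables section lists pTNM among the exposure variables, so it is a candidate predictor.

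On entry, the Study population section states: "The breast cancer diagnosis considered will be that reached after a biopsy of the tumor".

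**The concern.** Both rules replace an unknown with a specific value, and always with the favourable one.

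For stage, the result is partly illogical. Every woman enters with a biopsied breast tumour, so T0 (no primary tumour) cannot describe her at entry. Complete response to neoadjuvant therapy does not explain it either, because those women are staged on cTNM. NX to N0 merges nodes nobody assessed with nodes found negative, which dilutes any node effect.

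For complications, silence in a record that covers the period may well mean that nothing happened. Silence in a record with no contact in that period means nothing either way. The rule does not separate the two. It acts on an endpoint and on a prediction-model outcome. If completeness of records differs between sites, the sites with thinner records look safer, which bears directly on the objective of describing variation between hospitals, regions and surgeons.

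**Working it through.** **1. The staging rules side by side.** If pTNM and cTNM are both absent, stage is missing ("otherwise, missing value will be recorded"). If a component is X, it becomes zero. Both are cases of not knowing, and they are handled in opposite ways.

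**2. What Table 3 reveals.** Staged women, surgery: 135 + 683 + 453 + 134 + 18 = 1423 of 1432. No surgery: 0 + 2 + 5 + 4 + 11 = 22 of 24. Without a stage: 9 + 2 = 11 of 1456 (0.8%). How many of the other 1445 carry an assumed T or N cannot be seen.

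**3. Illustration for NX to N0.** From the article: overall relapse 4% (Sample size calculation). Assumed: true odds ratio 3.0 for node-positive against node-negative, and a node-positive share q = 30% among assessed women. These give relapse risks r0 = 2.57% and r1 = 7.34% (check: 0.7 × 2.57% + 0.3 × 7.34% = 4.0%). With x the share of NX and k the node-positive share among NX:

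recorded N0 risk = [(1−x)(1−q)r0 + x(1−k)r0 + x·k·r1] / [(1−x)(1−q) + x]

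For x = 10% and k = 30%: (0.70 × 0.02571 + 0.03 × 0.07335) / 0.73 = 0.02767, and the odds ratio against r1 is 2.78.

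| Share NX | k = 15% | k = 30% | k = 60% |
|---|---|---|---|
| 1% | 2.99 | 2.98 | 2.95 |
| 5% | 2.94 | 2.88 | 2.78 |
| 10% | 2.89 | 2.78 | 2.59 |
| 20% | 2.79 | 2.61 | 2.30 |

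The effect is always attenuation, and it is small if NX is rare.

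**4. Illustration for complications.** If a share u of women is undocumented, independently of the event, the recorded rate = true rate × (1 − u). A true 20% becomes 19%, 18%, 16% or 14% for u = 5%, 10%, 20% or 30%.

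**5. Two hospitals with the same true rate.** Assumed 200 women each (Table 2 lists several hospitals with 197 to 246), two-sided 5% test:

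| True rate | Undocumented | Recorded | Odds ratio | Chance of p < 0.05 |
|---|---|---|---|---|
| 20% | 5% vs 15% | 19% vs 17% | 1.15 | 7% |
| 20% | 5% vs 30% | 19% vs 14% | 1.44 | 27% |
| 30% | 5% vs 30% | 28.5% vs 21% | 1.50 | 41% |

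For the second row, (0.19/0.81) / (0.14/0.86) = 1.44. With no real difference, the last column should read 5%.

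**6. Would the planned analysis catch it?** The 60/40 random split applies the same recodes to both parts, so that internal validation cannot expose them. The multilevel model with patients within hospitals would absorb documentation differences as hospital effects.

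**The case against.** The case against a serious effect has substance.

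- **The complications rule presupposes a record.** The article plans follow-up visits at all 13 hospitals and says clinical data will be collected on women lost to follow-up. Intraoperative and in-hospital complications come from the index admission, so the exposure is mainly in the later windows. The dichotomous model outcome is major complications, which are arguably less likely to go unrecorded. A common handbook, supervision, a project manager at each hospital and monthly quality checks should narrow any gap between sites.
- **The cTNM fallback may work component by component.** An unassessed pathological N would then take the clinical N, and the zero would apply only if that is X too. The text allows this reading but does not settle it.
- **The numbers above are assumed.** The article gives no TX, NX or record-completeness figures.

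All of this limits the likely size. None of it removes the rules, which the article states outright rather than leaving to an analysis plan. The safeguards improve data collection but do not change what is done when information is absent, and the Problems anticipated section names difficulty in obtaining all required data as a main problem.

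Three stronger readings are tempting and should not be adopted.

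- A reader might take stage to be the leading predictor. The article lists it as one exposure among many and selects predictors by univariate p < 0.20.
- A reader might suppose that NX is concentrated in frail or non-operated women. The article does not say so. Only 24 women (1.65%) had no surgery; none is stage 0 and 11 are stage IV.
- A reader might infer that every lost or transferred woman is counted as complication-free. The rule does not expressly say that. It only lacks a condition that would prevent it.

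**Conclusion.** The point stands in two parts of unequal weight.

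The complications rule is the stronger. It has no condition that the record covers the window, so its error can only lower the rate of a named endpoint, and unequal documentation would appear as unequal outcome. These facts about direction do not depend on any assumed figure.

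The staging rule is internally inconsistent: T0 against a biopsied tumour, and X set to zero while a wholly absent stage is missing. It can weaken a candidate predictor, but only slightly if TX and NX are rare.

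The size of either bias cannot be computed from the article. The odds ratios and false-positive rates above rest on the assumptions stated with them and show a range, not an estimate. The point concerns T and N; it does not depend on the M recodes.

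**What to change.** - **Stage.** Where pathological T or N is X, use the analogous clinical component, and say so explicitly. If that is also X, code it as missing and multiply impute from variables already collected: tumour size, nodes analysed and positive, grade, receptors, age and outcome. The outcome belongs in the imputation for model fitting only, since it is unknown when the score is applied. For the bedside score, a separate unknown category is an acceptable alternative.
- **Complications.** Code none only when the record shows a contact covering that window. Otherwise treat the value as missing, or censor at last contact.
- **Transparency.** Flag each recoded value, so that assumed and documented negatives stay distinguishable, and report the counts by hospital. Keep the present rules as a sensitivity analysis.

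No new patient data are needed. The cost is slightly wider intervals and some extra analysis work. The change is best made before recoded values are stored without a flag.

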### Statistical analysis

- Descriptive statistics: Mean and standard deviations for continuous variables (or median and interquartile ranges, when the observed variables do not follow a normal distribution) and frequencies and percentages for qualitative variables.-Bivariate analysis:The Student’s t-test or the non-parametric Wilcoxon test (for non-normal distributions) will be applied for two-level outcomes, and ANOVA analysis or a Kruskal–Wallis test (for non-normal distributions) where there are three or more categories in the outcome. Otherwise, for categorical variables, the Chi-square test (or Fisher’s Exact method, where required) will be used. Multivariate models will be used where appropriate to adjust for confounders.-Creation and validation of predicitive models:. Participants will be randomly divided into two groups: the derivation (60%) and validation (40%) cohorts. The study unit will be the patient (each patient being included only once). The predictive model will be created with the derivation group (group 1). Initially, univariate analyses will be performed, to identify variables related to the selected outcomes. Variables with a *p* < 0.20 will be entered into a multivariate logistic regression model, when outcome variables are dichotomous (mortality, re-admissions or relapse, major complications). Statistically significant variables will be included in the final model. Based on its estimated contribution in the multivariate logistic regression model, a score will be assigned to each variable. From this, a severity risk score will be created with the receiver operating characteristic curve. One cut-off point will be selected, namely, that giving the best balance between sensitivity and specificity. For the continuous outcomes (changes in health-related quality of life), a general lineal model will be used. The validity of the model and the score will be tested in the validation sample (group 2) and also in the retrospective sample (group 3). We will calculate the sensitivity, specificity, and area under the receiver operating characteristic curve (AUC), and *p* values for comparisons of AUCs between the groups. The models will be calibrated using the Hosmer-Lemeshow test. A multilevel analysis will be performed with patients (level 1) nested within hospitals (level 2).

Cost analysis: The perspective of the cost analysis is that of a public hospital in a national healthcare system, and therefore, only direct medical costs (DMCs) will be included. DMCs will be derived from healthcare use registered in the medical records. Data on resource use will be obtained for the periods of 24 and 60 months after baseline, that is, since diagnosis. This includes data on medical visits; hospital admissions; laboratory tests, imaging studies, and other diagnostic procedures; and treatments including surgery, medication (chemotherapy and other) and radiotherapy. Little used and/or low cost resources will be not considered. The value of resources used by patients is to be calculated in terms of the relevant unit costs and the average cost per patient in the sample. The unit costs will be obtained for each resource from the accounting system of participating hospitals. Unit costs will be multiplied by the resource quantities to obtain the annual cost for each patient. All costs will be assigned in euros of the year in which the resource has been used; no discount rate will be needed due to the short time horizon.

Costs will be aggregated and classified according to the following categories: outpatient clinic visits (number of visits to specialists); hospitalization (total length of hospital admissions, length of stay in intensive care unit and day hospital visits); laboratory tests (laboratory tests performed through ambulatory care); and imaging studies (ultrasonography, axial computerized tomography, magnetic resonance, radiography and other imaging studies related to the diagnosis, and treatment and associated complications); diagnostic procedures (procedures related to the monitoring of the disease and associated complications); surgery (surgical procedures related to the treatment and associated complications); medication; radiotherapy.

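### The only unadjusted comparison rule given for non-normal variables is a rank test, and costs are not exempted, although the regional cost objective concerns average cost

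*Protocol article*

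**What the plan says.** Table 1 (Aim) sets the cost objective as "To estimate the average costs of breast cancer care in Spain", and the next item is differences between Spanish regions. The Aim text joins the two by asking how costs vary from region to region. The Cost analysis paragraph values resource use through unit costs and "the average cost per patient in the sample". The target is therefore a mean.

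The Statistical analysis section opens with a general rule. A continuous variable is described by its mean and SD, with this alternative: "or median and interquartile ranges, when the observed variables do not follow a normal distribution". Comparisons over two levels use a t-test, replaced by a Wilcoxon test if normality fails. Beyond two levels the rule is "ANOVA analysis or a Kruskal–Wallis test (for non-normal distributions) where there are three or more categories in the outcome". On adjustment, the section says only this: "Multivariate models will be used where appropriate to adjust for confounders". No variable is exempted.

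The Cost analysis paragraph comes under the same heading. It fixes perspective, resources, unit costs and cost categories, but names no test or model for comparing costs between regions or other groups. Design and setting gives four regions, so the three-or-more-groups branch would apply.

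**The concern.** Per-patient treatment costs are usually right-skewed, and this cohort gives reason to expect it. Table 3 shows stages 0 to IV, with 31.77% of surgical patients receiving adjuvant chemotherapy and 11.52% neoadjuvant therapy. An analyst who finds non-normal costs and follows the general rule arrives at Kruskal–Wallis.

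That test asks whether costs in one region tend to rank higher than in another. A health system pays the number of patients times the mean cost, and mean cost is what Table 1 names. The two questions coincide only in special cases, such as equal distribution shapes across regions. Table 1 also sets out to study variability in treatment and differences between regions, so equal shapes cannot be presumed.

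Two errors could follow. A regional cost difference could be reported where average costs are equal. A real difference in average cost could be missed when it comes from a costly minority of patients. The rule also makes the quantity compared depend on the observed shape of the data.

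**Working it through.** The article states no figure for the cost comparison, so there is none to reproduce. The check asks what the stated rule would do with the study's own region sizes.

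**Inputs from the documents (Table 2).**
- Catalonia: 97.
- Basque Country: 197 + 246 + 125 + 229 + 245 + 134 = 1176.
- Andalusia: 80 + 6 = 86.
- Canary Islands: 61 + 36 = 97.
- Total: 97 + 1176 + 86 + 97 = 1456, as stated.

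**Assumptions (not in the documents).** Costs are lognormal with log-SD s between 0.6 and 1.0, patients are independent, and tests use the 5% level. Each scenario has 4000 simulated data sets, so the simulation standard error is √(0.05 × 0.95 / 4000) ≈ 0.3 percentage points near 5% and √(0.68 × 0.32 / 4000) ≈ 0.7 points near 68%.

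**Why means and ranks part company.** A lognormal cost has median exp(μ) and mean exp(μ + s²/2).
- Equal means, s = 0.8 against 0.6: ratio of medians = exp(−(0.64 − 0.36)/2) = exp(−0.14) = 0.87.
- Equal means, s = 1.0 against 0.6: ratio of medians = exp(−(1.00 − 0.36)/2) = exp(−0.32) = 0.73.
- Equal medians, s = 1.0 against 0.6: ratio of means = exp(0.32) = 1.38.

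In the first two cases average costs are identical but ranks shift. In the third, average costs differ by 38% and ranks hardly shift.

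**Rejection rates.**

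| Scenario | Kruskal–Wallis | ANOVA | Welch ANOVA |
|---|---|---|---|
| Equal means, s = 0.8 in all regions | 4.9% | 5.4% | 8.0% |
| Equal means, s = 0.6 Basque Country, 0.8 elsewhere | 68% | 19% | 9% |
| Equal means, s = 0.6 Basque Country, 1.0 elsewhere | 99.7% | 34% | 13% |
| Equal means, s = 1.0 Catalonia, 0.6 elsewhere | 83% | 17% | 8% |
| Equal medians, Catalonia mean 38% higher (s = 1.0 against 0.6) | 8% | 85% | 37% |

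A smaller shape difference also matters: with equal means and s = 0.7 against 0.6 in the Basque Country, Kruskal–Wallis rejects about 24% of the time.

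**Reading the table.** In the four equal-means rows, any rejection is a false claim about average cost. Kruskal–Wallis is not malfunctioning, since the distributions do differ in three of those rows, but it answers another question. ANOVA and Welch target the mean yet also exceed 5% when skewed costs meet very unequal group sizes. ANOVA's 85% in the last row is therefore not clean power: with the same shapes and equal means it already rejects 17%. Replacing the rank test with a textbook means test would not be enough.

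**The case against.** The strongest reply is that nowhere does the article say costs will be tested on ranks. A reader might infer that the plan has chosen rank tests for regional costs, or that costs will be reported as medians. The documents support neither. The Cost analysis paragraph is a separate block that names average cost per patient as its summary, and that specific statement prevails over the general descriptive rule. The test rule is also worded for categories of the outcome, whereas here cost is the outcome and region the grouping factor. Multivariate models and a multilevel analysis are planned too. Finally, a journal article commonly leaves the test for one economic comparison to a fuller plan, and the sizes above rest on assumed distributions.

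Much of this stands. The cost estimate is protected, the use of ranks is a consequence of following the text rather than a declared choice, and the sizes are illustrative. With equal shapes the rank test is harmless.

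It does not remove the mismatch. The multivariate provision is not tied to costs, the general linear model is assigned to changes in quality of life, and the multilevel analysis sits with the prediction models. The loose wording about categories of the outcome is still the only unadjusted comparison rule given for a non-normal continuous variable. The point is a stated rule that does not fit a stated objective, not merely an absent detail.

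**Conclusion.** The point holds, confined to comparing costs between regions or other groups. The article's general rule, with no exemption, would send skewed costs to Kruskal–Wallis, which does not test the average cost that Table 1 and the Cost analysis paragraph name. The average-cost estimate itself is not at risk.

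The possible size is large but conditional. Under assumed lognormal costs with equal means and the Table 2 region sizes, rejection rises from about 5% with equal shapes to 68% at log-SD 0.8 against 0.6. In the other direction, a 38% higher mean in one region with equal medians is flagged only 8% of the time. The real figures depend on how far cost shapes differ between regions, on which the documents give no data. It is a cheap improvement worth making, not a flaw that invalidates the plan.

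**What to change.** Add two sentences to the Cost analysis paragraph. First, state that the normality rule in the Statistical analysis section does not govern cost comparisons. Second, state that regions and other groups will be compared by differences in arithmetic mean cost, using a method suited to skewed costs. That could be bootstrap intervals, or a gamma model with log link adjusted for stage and age, allowing for clustering by hospital in either case. Medians and interquartile ranges may stay as description. Plain ANOVA or Welch tests should not be the substitute, for the reason shown above.

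The change needs no new data. Its price is wide intervals for mean cost in the small regions (86 to 97 women each), which is a fair picture of what the sample can say about them.
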